## Abstract

**Introduction:**

People with body mass index (BMI) ≥35 kg/m^2^ have an approximately 19-fold increased risk of undergoing total knee replacement (TKR); however, many UK integrated care boards (37%) have restrictive policies which limit access to TKR for people based on BMI. Therefore, access to both surgical and non-surgical treatments varies widely, exacerbating existing health inequalities. It remains unclear how decisions about offering TKR are made in people with severe knee osteoarthritis, which weight-loss interventions are provided in practice and how different management pathways relate to patient outcomes among individuals with high BMI.

**Methods and analysis:**

This study will recruit 400 participants with severe Kellgren-Lawrence grade four knee osteoarthritis from eight secondary care centres in England. All participants, irrespective of BMI, will provide baseline clinical data and patient-reported outcome measures (PROMs), enabling characterisation of baseline associations between BMI, knee function and body image.

A prespecified subgroup of participants with BMI ≥35 kg/m^2^ (minimum n=105) will undergo longitudinal follow-up at 6 months, 12 months and 24 months, including repeat BMI measurement, PROMs and detailed data on access to surgical and non-surgical interventions, including weight-loss strategies and TKR. For those with BMI ≥35 kg/m^2^, statistical modelling will be used to explore associations between baseline factors and longitudinal outcomes including Oxford Knee Score and weight change at 12 months (n≥105). Structural equation modelling will be used to quantify associations between BMI and knee pain/function mediated by psychosocial factors using data from all participants (n=400). A nested qualitative study of surgeons and patients will explore obstacles and preferences in the management of severe knee osteoarthritis.

**Ethics and dissemination:**

The study received ethical approval from the West of Scotland REC 5 (Ref: 24/WS/0146) on 10 October 2024. Results will be disseminated through peer-reviewed publications.

**Trial registration number:**

ISRCTN42984928.

STRENGTHS AND LIMITATIONS OF THIS STUDYProspective observational study that includes participants from eight heterogeneous sites covering a diverse local population across England aims to provide representative sample which reflects National Health Service service variation.Collection of routine patient-reported outcome measures (PROMs) (Oxford Knee Score and Euro-Qol Five Dimensions) in addition to broader PROMs not routinely collected (Activity Participation Questionnaire, General Self-efficacy scale and Body-Q).Addition of exploratory qualitative and quantitative analyses to the main cohort study.Does not examine primary care practices or include those with severe arthritis and obesity who do not get referred to secondary care.Can identify associations but cannot measure causal relationships between treatments and outcomes.

## Introduction

 Knee osteoarthritis (OA) affects approximately 4.5 million adults over the age of 45 years in England.^1^ Severe knee OA represents a major cause of pain, disability and referral to secondary care and is managed through a combination of non-surgical interventions and, for some patients, progression to total knee replacement (TKR). The pathophysiology of OA involves mechanical factors and pro-inflammatory mediators, which are both exacerbated by obesity.^2 3^ Obesity, defined by the WHO as a body mass index (BMI) of ≥30, leads to greater loading forces in the articular cartilage which can lead to tissue damage after prolonged exposure and also leads to greater presence of pro-inflammatory mediators.^4^ As a result, people with a BMI of ≥30 kg/m^2^ have 4.6 times increased risk of developing knee OA when compared with people with a BMI of <25 kg/m^2^.^5^ The risks rise steeply with higher BMI: those with a BMI of 35–39.9 kg/m^2^ have an 18.7-fold increased risk of having a TKR. This group is therefore not only at greater clinical risk but also disproportionately affected by restrictive BMI-based thresholds for accessing surgery, with 15/41 integrated care boards imposing BMI restrictions on joint replacement eligibility in England.^6^ As the proportion of adult obesity in England has increased from 14.9% to 28% since 1993, the burden of knee OA is expected to rise further.^7 8^

Greater BMI is associated with greater pain from knee OA irrespective of radiographic severity.^9 10^ The causes of greater pain in obese individuals are multifactorial and include increased mechanical loading of the joint,^11^ a pro-inflammatory state through increased inflammatory markers such as interleukin-6 and C reactive protein^12^ and the complex reciprocal relationship between obesity, pain and depression.^13^

It remains unclear which non-surgical treatments should be offered to people with obesity and end-stage knee OA in secondary care if surgery must be delayed. Uncontrolled arthritis in this population has a substantial impact on well-being and has economic consequences. A 2021 Markov analysis has estimated over £100 000 in lost earnings in those with uncontrolled OA pain compared with those with controlled symptoms.^14^ The long-term outcomes for people who are denied a TKR due to high BMI are poorly understood, but previous work has shown that restrictive BMI policies are more likely to impact those with BMI ≥35 kg/m^2^.^15^ Furthermore, an American observational study of 125 patients denied a joint arthroplasty due to high BMI found that 80% of participants denied a joint arthroplasty failed to lose sufficient weight to subsequently be offered a joint arthroplasty, but the study had a high loss to follow-up rate of 62%.^16^

To address these evidence gaps and develop more standardised guidance for managing this population, we first need a clearer understanding of current care pathways, the treatments people receive and the factors influencing their outcomes. This protocol describes a prospective cohort study designed to characterise management pathways and outcomes in people with severe knee OA, with focused longitudinal follow-up of individuals with BMI ≥35 kg/m^2^, to inform future trials and evidence-based management strategies.

### Study aim

To examine management pathways and longitudinal outcomes in people with BMI ≥35 kg/m^2^ and severe knee OA referred to secondary care and to characterise baseline patient-reported outcomes across BMI categories.

Objectives:

Explore and model to what degree the interactions between baseline factors described in the prior objective, treatments received after recruitment and weight change predict knee function at 12 months after presentation to secondary care in this population.Qualitatively explore patient and surgeon experiences of treatments for high BMI and knee pain.Describe and quantify the relationship between underlying constructs measured by key patient-reported outcome measures for both obesity and knee-related pain and function at baseline across BMI categories.

## Methods and analysis

### Setting and participants

Participants will be recruited from eight secondary referral centres in England:

University Hospitals Coventry & Warwickshire.The Princess Alexandra Hospital NHS Trust.Luton and Dunstable University Hospital.Milton Keynes University Hospital.University Hospitals Birmingham.South Tees Hospitals NHS Trust.Wrightington, Wigan and Leigh NHS Foundation Trust.Northumbria Healthcare NHS Trust.

Recruitment commenced on 17 December 2024 and completed on 19 December 2025.

Inclusion criteria

Referral from primary care to secondary or intermediate care services for knee OA.Severe arthritis as assessed by the treating clinician. Defined as Kellgren-Lawrence grade four primary knee arthritis (severe) in any knee compartment on a knee radiograph (X-ray), or clinician deems arthritis severe enough to warrant a TKR.Aged over 18 years

Exclusion criteria

Presence of inflammatory arthritis.History of intra-articular fracture causing post-traumatic arthritis.Previous surgery on the ipsilateral knee if implants were inserted.Unable or unwilling to comply with follow-up procedures.Unable to provide informed consent (eg, does not have capacity to consent).Insufficient English language skills to understand study materials and respond to questionnaires.

### Study Procedures

Orthopaedic secondary care clinic lists will be screened to identify potential participants meeting the inclusion criteria. Approaches for recruitment will occur at their clinic appointment or via contact afterwards. Informed consent will be obtained, and a baseline questionnaire administered. Baseline data from participants with BMI <35 kg/m^2^ are required in addition to the baseline data from those with BMI ≥35 kg/m^2^ to allow cross-sectional modelling of BMI-related associations for all participants. Participants will continue with NHS treatment as deemed appropriate by their clinician. Longitudinal follow-up will be intentionally restricted to participants with BMI ≥35 kg/m^2^, in whom variability in access to care, mandated weight-loss interventions and delays to surgery are most pronounced. It is anticipated that some participants will undergo surgical intervention, including TKR, during follow-up, while others will remain on non-surgical management pathways, but this will be collected as part of follow-up. Follow-up will occur at 6 months, 12 months and 24 months via telephone, post or email for participants where BMI ≥35 kg/m^2^. Weighing scales will be offered to those without access to scales at home.

### Participant identification and screening

Potential participants will be screened and identified for eligibility by the site clinical teams by inspecting lists in secondary or intermediate care clinics at each of the study recruitment sites. Potential participants will be approached via telephone or in person and invited to discuss the study. Written study information may be posted to them. Potential participants will be encouraged to contact the research team directly by telephone or email after reading the study information sheets, which will be posted to them, to indicate their interest in participating in the study. A member of the local research team will carry out the informed consent process, enrolment and baseline data collection. Height and weight data will be collected by a member of the research team in person or where documented on the participant’s electronic record within the last 2 months.

All people who meet the study entry criteria will be checked for eligibility and recorded on the monthly screening log. Screening log data for participants who meet the eligibility criteria and decline to participate will include: age, sex and ethnicity.

### Baseline data collection

The baseline questionnaire will include:

Height and weight, which will be used to calculate BMI. This will be measured and recorded by a member of the research team or extracted from the electronic record if measured within the preceding 2 months.Oxford Knee Score (OKS), a patient-reported outcome measure (PROM) with 12 items, each of which is scored on an ordinal scale from 0 to 4 and totalled to give an overall assessment, that was developed for assessing outcomes after TKR.^17 18^ It has been extensively validated^19^,^21^ and its psychometric properties described previously^22^ and is the core measure used in the UK National Joint Registry (scoring 0–48; 0=worst possible score, 48=best possible score).OKS-Activity Participation Score (APQ) was developed as an adjunct to the OKS. The purpose of the APQ is to combat potential ceiling effect for OKS when used alone in a postoperative population^23^ (0=worst possible score, 100=best possible score).Body-Q, a PROM which was developed for use by people with obesity undergoing weight loss interventions. It measures four domains (appearance, eating-related concerns, health-related quality of life and experience of care). An international multidisciplinary consensus meeting identified which constructs were most important to measure and identified BODY-Q as the PROM instrument which best measured six out of eight of the most important domains.^24^ Two subscales will be used: body image and appearance-related psychosocial distress. For both subscales, 0=worst possible score, 100=best possible score (Rasch scaled scores).Euro-Qol-Five Dimensions-5 Levels (EQ-5D-5L) is a measure of health-related quality of life that assesses mobility, self-care, usual activities, pain/discomfort and anxiety/depression (five dimensions).^25 26^ The value set for England developed by Delvin *et al*^27^ will not be used as it was rejected by the National Institute for Health and Care Excellence (NICE).^28^ Instead, the scores will be mapped onto the 3L value set,^29^ unless the NICE guidance changes regarding this, reported as an index score −0.594 (worst score)–1 (best score) and anchored at 0 (death). A Visual Analogue Scale score (0=worst score, 100=best score) also forms part of EQ-5D-5L and provides a complementary patient-reported measure of overall health status.Generalised Self-Efficacy scale^30^: a questionnaire used to quantify a person’s perceived ability to cope with adversity, where 10=worst score and 40=best score.Hospital Anxiety and Depression Scale.^31^ A scale which quantifies depression and anxiety in medical patients. Scored from 0 to 21 for each of the anxiety and depression subscales, where 0=best score (no anxiety or depression) and 21=worst score (severe distress).

### Follow-up assessments

The follow-up questionnaire will collect data on participants’ weight, weight-loss treatments that participants have received and treatments for their knee and their outcomes.

At 6 months, 12 months and 24 months, the same PROMs collected at baseline (OKS, APQ, Body-Q, EQ-5D) will be readministered, with the addition of the Global Rating of Change Scale.^32^ This is a seven-point scale ranging from ‘no change or condition has worsened’ to ‘a great deal better’. This will provide a reference point against which changes in other PROMs can be interpreted, helping to distinguish meaningful improvement from measurement variability.

Participants will additionally be asked the following questions about previous knee treatments at each follow-up assessment: have they had a knee replacement or other knee surgery, physiotherapy and/or a steroid injection in the last 6 months and/or are they on a waiting list for knee replacement surgery.

Participants will also be asked about weight loss treatments including whether they have had weight loss surgery, taken prescribed medications for weight loss, attended an NHS-referred structured weight loss programme or dietary modification programme and/or they meet the minimum NHS-recommended exercise recommendations.

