### Primary outcome and analysis timepoint

The primary outcome for this study is change in OKS from baseline to 12 months. A 12-month period has been selected as the prespecified time point for the main analysis, as it represents a clinically meaningful period in which to assess functional change and weight management interventions, while also minimising loss to follow-up.

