### Statistical analysis

Descriptive statistics will be used to summarise the demographic and questionnaire data at baseline and follow-up. Means and SD for continuous and assumed continuous variables (eg, age and PROMs) and counts and percentages for categorical variables (eg, gender). Treatments for both the knee and weight management will be categorised according to NICE OA^37^ and obesity^38^ guidelines, offered and delivered and what proportion of participants complies with each of the treatment options as defined above.

A longitudinal linear regression model will be fitted using all available longitudinal data from participants with BMI ≥35 kg/m^2^ to determine the variables which predict the primary outcome (OKS) at 12 months after first presentation to secondary care. The explanatory variables will include those data collected at follow-up time points (EQ-5D, BMI change, adherence to treatments as described above, receiving TKR, BODY-Q score). In order to assess the veracity and stability of the fitted model, sensitivity analyses and a number of standard methods will be investigated for imputing missing values (eg, multivariate imputation by chained equations using mice package in R).^39^ All analyses will be performed in R with significance set at the 5% level.^40^

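### A fixed six-month look-back for knee treatments, with visits at 6, 12 and 24 months, leaves months 12–18 unasked about, so 24-month counts of non-surgical treatment will be too low

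*Protocol article*

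**What the plan says.** The Study Procedures section sets the schedule for participants with BMI of 35 or more: "Follow-up will occur at 6 months, 12 months and 24 months via telephone, post or email".

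The Follow-up assessments section puts the same knee items on every form: "Participants will additionally be asked the following questions about previous knee treatments at each follow-up assessment". The list opens with surgery ("have they had a knee replacement or other knee surgery") and ends with "physiotherapy and/or a steroid injection in the last 6 months and/or are they on a waiting list for knee replacement surgery". It gives no longer window for the 24-month form and no wording tied to the previous contact. The weight-loss items beside it carry no stated window ("whether they have had weight loss surgery, taken prescribed medications for weight loss").

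Treatment data are used in two ways. The Statistical analysis section plans a description of knee and weight treatments offered and delivered. It also lists the follow-up variables in the regression for 12-month Oxford Knee Score: "EQ-5D, BMI change, adherence to treatments as described above, receiving TKR, BODY-Q score". The primary outcome is fixed at 12 months: "The primary outcome for this study is change in OKS from baseline to 12 months". The Long-term outcomes section makes the 24-month questionnaires and the linkage to the National Joint Registry (NJR) and Hospital Episode Statistics (HES) secondary, and reports them apart from the 12-month results.

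**The concern.** The look-back matches the visit spacing for the first two forms but not for the third, which comes 12 months after the second. A participant who has a steroid injection in month 14 can truthfully answer no at 24 months, although the 24-month scores may still reflect that treatment.

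The study sets out to describe how people with high BMI and severe knee osteoarthritis are managed over time, so the record of treatments received is one of its main products. Non-surgical care is where the article sees the evidence gap, and it is also the care for which no second data source is named. If the item stays as it is, the second-year picture will show less non-surgical treatment than was given, and nothing in the data will reveal the shortfall.

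**Working it through.** **Inputs.** Visits at 6, 12 and 24 months (Study Procedures). Look-back of 6 months on each form (Follow-up assessments). Recruitment from 17 December 2024 to 19 December 2025 (Setting and participants). Planned numbers of 76, 84 and 105 (Sample size calculation).

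**1. Coverage when every form is returned.** A form at month v with look-back w covers the interval from v − w to v. With w = 6:

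| Form | Months covered |
|---|---|
| 6 months | 0–6 |
| 12 months | 6–12 |
| 24 months | 18–24 |

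Together these cover 18 of 24 months. The gap is months 12–18: 6/24 = 25% of follow-up time, and 6/12 = 50% of year two. Months 0–12 are covered without a gap, so the 12-month analysis is complete for anyone who returns both early forms.

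**2. Which items the gap touches.** The six-month phrase closes a list, and its reach can be read in three ways:

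- It governs the whole list (the natural reading): surgery, physiotherapy and injection all have the gap.
- It governs physiotherapy and injection only: surgery is asked without a window.
- It governs injection only: injection alone has the gap.

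The injection gap is present on all three readings. Waiting-list status is a current-state question, so no window applies to it.

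**3. Coverage after the change.** If the 24-month form reaches back to the 12-month form, the windows are 0–6, 6–12 and 12–24, and no month is left out.

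**4. A missed 6-month form (secondary point).** The 12-month form alone covers months 6–12, so 6 of the 12 months before the primary time point are unasked about. The number affected depends on how many people miss the 6-month form but return the 12-month one, and the article does not state that rate. The planned number analysed is reproduced from the article's own figures: 76 × 1.1 = 83.6, rounded up to 84, and 84/(1 − 0.20) = 105. Assuming that 5% to 20% of the 84 missed the 6-month form gives 0.05 × 84 = 4.2 to 0.20 × 84 = 16.8, or about 4 to 17 people.

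**5. Timing.** The 24-month forms fall due from December 2026 to December 2027. The 6-month forms fell due from June 2025 and the 12-month forms from December 2025.

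**The case against.** The strongest reply is that little of this reaches the main result. That is right. For people who return both early forms the windows meet exactly over 0–12 months, and the only outcome model described is at 12 months.

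Four stronger readings are tempting, and the document does not support them:

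- **That the look-back damages the primary model.** What remains there is ordinary missingness from an unreturned form, and the Statistical analysis section plans sensitivity analyses and imputation. Imputation does not observe the lost treatments, but this is no contradiction in the plan. It becomes a real error only if a no at 12 months is taken to cover the whole year.
- **That one in five would lack months 0–6.** The article's 20% is loss to follow-up, meaning people who leave the analysis. It is not the rate of missed 6-month forms among those who stay.
- **That an operation in month 14 would be recorded as no surgery.** This depends on where the six-month phrase attaches. NJR and HES linkage may also recover the operation and its date. The article describes linkage as reaching past 24 months, which does not rule out its use for earlier operations.
- **That a quarter of treatments would go unrecorded.** This needs a constant treatment rate, for which the article gives no support. It also counts episodes, not people. The item is yes or no, so someone treated repeatedly may be captured in another window.

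It can also be said that this is a condensed article and the questionnaire may word the 24-month item differently. That is possible. But the article is not silent: it states a window and applies it at every follow-up. If the form differs, the article should be corrected.

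**Conclusion.** The point holds in limited form. As written, months 12–18 fall outside every look-back, which is 6 of 24 months and half of year two. This follows directly from the stated schedule and window, and rests only on the forms matching the article. The consequence is an undercount of steroid injections, and on the natural reading of physiotherapy, in the 24-month description and in any 24-month comparison of pathways. The size of that undercount in people cannot be derived, because the article gives no treatment rates.

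Knee replacement is probably recoverable through linkage, although the plan does not say that linkage will be used this way. The gap does not touch the 12-month primary analysis. The missed 6-month form is a separate and smaller coding matter, affecting about 4 to 17 of 84 participants on an assumed rate of 5% to 20%.

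**What to change.** 1. On the 24-month form, change the look-back for all knee-treatment items to *since your last completed study questionnaire*, or since joining if none was returned. At minimum, use *in the last 12 months*. Asking since the last completed questionnaire is better because it also covers a missed 12-month form. Place the time phrase so that it plainly governs surgery, physiotherapy and injection alike.
2. State that NJR and HES linkage will be used to confirm knee surgery and its date within the 24 months, as well as afterwards.
3. State in the analysis plan that, for a participant who missed the 6-month form but returned a later one, treatment in months 0–6 is missing and not absent. A no on the 12-month form then applies to months 6–12 only.

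The 12-month form is better left alone. Some fell due from December 2025, so a change now would give early and late recruits different wording within the primary analysis.

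**Cost.** A small change to one questionnaire and a minor amendment, in place before the first 24-month forms in December 2026. Recall lengthens from 6 to 12 months for most participants, and further for those who missed the 12-month form, so some treatments will be forgotten or misdated. The alternative is never to ask about those months. The change concerns data collection only and leaves clinical care as it is.
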